**i) Suspected unexpected serious adverse reaction**

As a minimum requirement Serious Adverse Events which are unexpected and related (SUSARs) and Adverse Events which may constitute hazard or safety of subjects recruited in the project shall immediately be reported by the Investigator to the EC, the local Health authority and to the respective local company if applicable.

According to valid regulatory requirements, the respective company has to collect, assess and report Adverse Events, noted in connection with the use of the company products. Therefore, the Investigator shall notify the respective company about all Adverse Events after completion of the project.

#### **7.4 Type and duration of the follow-up for subjects after adverse events**

Participants of the trial will be treated according to the physician's judgement. The measures and the outcome of an adverse event (until the end of the follow-up stated in the protocol) have to be documented using the corresponding forms.

#### **7.5 Report of serious adverse events**

The investigator is responsible to report all serious adverse events (SAEs) within 24 hours by telephone or fax using a SAE report form to the respective drug company.

The initial SAE report should contain the following details: study number, patient number, initials, sex, date of birth, drug allocation, date of onset, description of the event, name, address and telephone number of the investigator.

The investigator is responsible to inform the Ethics Committee of SAEs on an ongoing basis.

The single case documentation of a serious adverse drug reaction, an interaction or an observed, relevant abuse is a report, which has to be submitted within 24 hours by telephone or fax using a SAE report form to the respective drug company. This report is required, if - in relationship with the administration of a drug - an event occurs, which causes a serious reaction (in the sense of the above definition) in a patient.

Following information is considered to be minimal criteria for a single case documentation:

- identified patient;
- suspected drug;
- observed serious adverse drug reaction or interaction/abuse;
- identified data source.

Adverse events, which are not serious, are summarized at the end of the trial in the medical report, but will not be documented on the single case form or reported to the responsible authorities.

Acute steroid sensitive rejections are not considered as serious adverse events despite necessity of hospitalisation, because the events are expected during such a trial. Nevertheless, acute steroid resistant rejections will be notified to the health authorities.

## 8. ASSESSMENT OF EFFICACY

See 4.3.2 Secondary endpoints

## 9. STATISTICS

In this pilot study all statistical analyses will be descriptive and p-values will be interpreted accordingly. Confidence intervals will be provided to assist the interpretation of the observed effects.

The primary analysis of safety will assess the incidence of adverse drug reactions (ADRs) attributable to the investigational treatments according to the causality assessment detailed in Section 7.3, paragraph G. A separate analysis will be performed for each of the ADRs listed in Section 4.3.1 as well as for a summary of all ADRs not included in this compilation.

For comparison between ATG and Thymoglobulin the risk ratio (ratio of proportions of patients reporting a particular ADR at least once under trial drug and reference treatment) and the risk difference (difference between proportions) will be determined, including their 95% confidence intervals determined according to the method described by Newcomb (25). For comparisons between the AE rates under both treatments, descriptive two-sided p-values will be determined with Fisher's exact test. In a working definition, the following findings will be considered to be indicators of a potentially meaningful treatment group difference regarding ADR incidence:

- two-sided p-value  $\leq 0.15$  for the comparison of AE rates,
- risk ratio  $\geq 0.5$  or  $\leq 2.0$ ,
- 95% confidence interval for a risk ratio which excludes the value 1.0, and
- 95% confidence interval for a risk difference which excludes the value 0.0.

All analyses of safety will be performed primarily in the safety data set which includes all patients who have received the investigational treatment at least once. To assess potential bias introduced by premature withdrawal from the trial a sensitivity analysis will be performed in a subset which includes all patients who complete the follow-up period as scheduled (but independently of the presence or absence of protocol violations).

For the analysis of treatment efficacy actuarial life tables will be computed for the following parameters: graft survival, patient survival, time to first rejection episode. All life tables will be based on a period of observation of 24 months.

---

 Relevance criteria derived from (26).

In addition, inferential statistics will be computed for the following parameters:

- Time to 1st and 2nd rejection (Mann-Whitney U-Test).
- Incidence of rejection episodes (Chi-square statistic).
- Number of rejections per patient (Mann-Whitney U-Test).
- Duration of rejection episodes (t-test).
- 12, and 24-months graft survival rate (Chi-square statistic).
- 12 and 24-months patient survival rate (Chi-square statistic).
- Number of prednisone pulses within 12 and 24 months (Mann-Whitney U-Test).
- Rejection reversal rate (Chi-square statistic).

The analysis of efficacy will be based on the full analysis set (FAS) which includes all patients who were randomized and treated and for whom any post-treatment efficacy data are available.

After completion of the 24-months follow-up period the final biometrical analysis will be performed.

Furthermore, all patient data recorded in the trial database will be tabulated by treatment group using methods of descriptive data analysis, with specification of summary statistics applicable to their levels of measurement.

Sample size estimation:

In this pilot study the determination of the sample sized is based primarily on feasibility rather than on statistical reasons. A total of 40 (Zürich 20, Basel 20) randomised and treated patients (20 in each treatment group) will be included.

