#### **4.4 Time schedule**

The recruitment will start in November 2008. The enrolment will continue approximately 24 months until the desired patient number is reached, followed by a 12- month observation period.

Duration of treatment for:

ATG-Fresenius S: 5 days (per protocol)

Thymoglobulin: 4 days (per protocol)

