#### **4.5 Discontinuation criteria**

##### **a) Individual subjects**

Reasons for the discontinuation of the treatment of single patients during or after the study are:

- withdrawal of Informed Consent;
- evident lack of compliance of the patient;
- onset of HIV during the trial period;
- pregnancy;
- not permitted co-medication if it is a safety risk for the patient;
- relevant protocol deviation if it is a safety risk for the patient;
- severe surgical complications during the transplantation if it is a safety risk for the patient;
- lost to follow-up;

Whenever possible, patients in whom the investigational treatment is discontinued prematurely will be followed up until the scheduled end of the period of observation. Unless a patient withdraws his/her informed consent, is lost to follow-up or continued study participation presents an intolerable risk, withdrawal from treatment does not lead to withdrawal from the scheduled examinations or from the trial.

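### Time to rejection is compared with a test that ignores censoring, and the check for withdrawal bias keeps only completers; unequal loss to follow-up would mislead both

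*Protocol*

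**What the plan says.** Section 9 lists, among the inferential statistics, time to first and second "rejection (Mann-Whitney U-Test"). It gives no rule for patients who never reject or who leave early.

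The same section says that "actuarial life tables will be computed for the following parameters: graft survival, patient survival, time to first rejection episode", and "All life tables will be based on a period of observation of 24 months". Second rejection has no life table, and no log-rank or similar comparison is named. Survival at fixed times is tested separately: "12, and 24-months graft survival rate (Chi-square statistic"), and likewise for patient survival.

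For safety, the primary set is every patient treated at least once. To examine bias from premature withdrawal, a "sensitivity analysis will be performed in a subset which includes all patients who complete the follow-up period as scheduled".

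Incomplete follow-up is foreseen: "lost to follow-up" is one of the listed reasons in section 4.5. Section 4.4 describes about 24 months of enrolment "followed by a 12- month observation period", whereas section 9 analyses outcomes at 24 months.

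**The concern.** A patient who has not rejected has no rejection time, only a time up to which rejection was absent. Mann-Whitney cannot use that information. It must either rank the last observed time as if it were a rejection, so that a patient lost at month 2 looks like an early rejecter, or leave such patients out and compare only those who rejected. The chi-square tests of 12- and 24-month survival have a related gap, because a patient without known status at that time cannot be classified.

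The completer analysis has a different fault. Withdrawal for adverse events or other safety reasons is a component of the primary endpoint (section 4.3.1, item 4). A patient who leaves the trial for that reason has an event and is then removed from the analysis meant to show what withdrawal did to the result.

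At stake are misleading descriptive p-values for rejection and an uninformative robustness check on the primary safety result.

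**Working it through.** **Inputs.** From the protocol: 20 patients per arm, set by feasibility with no power or effect size attached, so there is no planned figure to reproduce. Background rejection rates in section 2.2.4 run from 29% (high-risk series) to 58-67% (randomised comparison). The protocol gives no dropout rate, so all loss rates below are assumptions. Tests are two-sided at 0.05.

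**Model 1: constant hazard, rate = -ln(1-p)/12 per month.**

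True difference, 20% vs 50% rejection at 12 months, complete follow-up. Expected rejecters are 20 × 0.20 = 4 and 20 × 0.50 = 10.
- Log-rank: power about 0.53 (0.53-0.56 across runs).
- Mann-Whitney on all 40, non-rejecters tied at the last rank: about 0.51.
- Mann-Whitney on rejecters only: 0.03-0.04.

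No true difference, 25% rejection at 12 months, 24 months of follow-up, Mann-Whitney on observed times:

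| Assumed loss, arm vs arm | False-positive rate |
|---|---|
| 10% vs 10%, months 0-6 | about 0.04 |
| 20% vs 20%, months 0-6 | 0.053 |
| 5% vs 15%, months 0-6 | 0.07-0.08 |
| 0% vs 25%, spread over 24 months | 0.12-0.13 |
| 0% vs 25%, months 0-6 | 0.24-0.25 |
| 0% vs 35%, months 0-6 | 0.41-0.42 |

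Log-rank gives 0.056 and 0.043 in the last two rows. With 2,000 runs the simulation error near 0.05 is √(0.05 × 0.95 / 2000) ≈ 0.005.

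**Model 2: early-weighted rejection (Weibull, shape 0.5), 24 months, loss uniform over 24 months, 4,000 runs.**

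| Rejection at 24 months | Assumed loss | Mann-Whitney, observed times | Log-rank |
|---|---|---|---|
| 30% vs 30% | none | 0.043 | 0.046 |
| 30% vs 30% | 10% vs 10% | 0.049 | 0.053 |
| 30% vs 30% | 5% vs 25% | 0.112 | 0.048 |
| 30% vs 30% | 0% vs 40% | 0.312 | 0.043 |
| 30% vs 60% | none | 0.48 | 0.51 |
| 30% vs 60% | 10% vs 10% | 0.42 | 0.49 |
| 30% vs 60% | 25% vs 5% | 0.21 | 0.49 |
| 30% vs 60% | 40% vs 0% | 0.09 | 0.47 |

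The first four rows are false-positive rates and the last four are power. In the last two rows the heavier loss is in the arm with less rejection: its short censored times pass for early rejections and hide the difference. Mann-Whitney on rejecters only has power 0.04-0.055 in the 30% vs 60% rows.

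**Second rejection.** At 30% first rejection, 20 × 0.30 = 6 patients per arm reject. If 30% of them reject again (assumption), 6 × 0.30 = 1.8 per arm do so, too few for any test.

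**Follow-up length.** If observation ends 12 months after a 24-month enrolment, a patient enrolled at month x has 36 - x months, which reaches 24 only when x ≤ 12. With even enrolment, about half of the 40 would lack a 24-month status. If each patient is followed for 12 months, none would have one. If each is followed for 24 months, as the month-24 blood work in section 6.2 suggests, there is no administrative censoring at that point.

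**Completer set.** Suppose the true incidence is 10/20 in both arms and four patients with events leave one arm. Completers then show 10/20 = 50% against (10 - 4)/(20 - 4) = 6/16 = 37.5%. The 12.5-point gap comes from selection alone. In the all-treated set both arms still show 10/20, provided the events were recorded before exit.

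**The case against.** The strongest reply is that little depends on these analyses. Section 9 declares everything descriptive, the trial is a 40-patient feasibility pilot with a safety primary endpoint, and section 4.3.2 lists rejection incidence, which has its own chi-square test, rather than time to rejection. Life tables already describe first rejection and survival. Under section 4.5, stopping treatment does not end scheduled examinations, which limits loss. All of this stands and lowers the severity. It does not supply a censoring-aware comparison or rescue the completer check.

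A reader might infer three stronger things that the protocol does not support.

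- That the rejection test has almost no power. This holds only if non-rejecters are dropped, which fits poorly with the full analysis set that section 9 prescribes for efficacy. With everyone included and followed, the loss of power is small.
- That false-positive rates of 25% to 40% are to be expected. They need heavy early loss in one arm and none in the other. Balanced loss does not inflate the error.
- That the safety result itself is distorted, or that the completer analysis will reassure whatever the truth. The primary safety analysis keeps all treated patients, completers with reactions still count, and a gap between the two analyses would be visible.

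**Conclusion.** The point holds as something that should be fixed, not as a critical flaw. The named test for time to rejection does not handle censoring, and no test that does is named. Its harm ranges from negligible (complete or balanced follow-up) through a false-positive rate of about 0.07-0.13 (moderately unequal loss, or one-sided loss spread over 24 months) to 0.24-0.42 (heavy one-sided early loss). Log-rank stays near 0.05 throughout. Those sizes rest on assumed loss rates and on the two rejection-time models above; the protocol supplies neither.

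Separately, a completers-only subset cannot assess bias from withdrawal, because it removes the patients concerned, including those who leave the trial for safety reasons. That weakens a sensitivity analysis only. Since results are descriptive, the consequence is misleading estimates and p-values rather than a failed confirmatory test.

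**What to change.** In section 9:

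- For time to first rejection, replace Mann-Whitney with a log-rank test in the full analysis set, alongside the planned life tables. Report second rejections descriptively.
- Take 12- and 24-month graft and patient survival, with 95% confidence intervals, from the life-table or Kaplan-Meier estimates instead of chi-square on crude proportions.
- Replace or supplement the completer subset with an analysis of all treated patients: time to first primary event censored at withdrawal, plus a worst-case count in which early leavers are taken to have had an event.
- Reconcile the 12-month observation period in section 4.4 with the 24-month analyses in section 9, since this determines how much censoring there will be.

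The cost is a few lines of text and slightly more programming. The planned life tables already need dates of first rejection, graft loss and death, and section 7.3 requires the timing of each adverse event to be recorded; the case report form is not shown, so this should be confirmed there. Results remain descriptive, and 20 patients per arm still gives only about even power for a difference as large as 30% vs 60%.

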### 2.4.3 Clinical trials

A controlled, double-blind, multicenter, randomized clinical trial by GABER et al. (1) comparing Thymoglobulin and ATGAM was conducted at 28 US transplant centers in renal transplant patients (n=163) with biopsy-proven Banff Grade II (moderate), Grade III (severe), or steroid-resistant Grade I (mild) acute graft rejection. This clinical trial rejected the null hypothesis that Thymoglobulin was more than 20% less effective in reversing acute rejection than ATGAM. The overall weighted estimate of the treatment difference (Thymoglobulin-ATGAM success rate) was 11.1% with a lower 95% confidence bound of 0.07% (27).

In the study, patients were randomized to receive 7 to 14 days of Thymoglobulin (1.5 mg/kg/d). For the entire study, the two treatment groups were comparable with respect to donor and recipient characteristics.

There were no significant differences between the two treatments with respect to day 30 serum creatinine levels relative to baseline, improvement rate in post-treatment histology, one-year post-rejection Kaplan-Meier patient survival (Thymoglobulin 93%, n=82 and ATGAM 96%, n=80), day 30 and one-year post rejection graft survival (Thymoglobulin 83%, n=82; ATGAM 75%, n=80).

Thymoglobulin adverse events were generally manageable or reversible. In the US Phase III controlled clinical trial (n=163) comparing the efficacy and safety of Thymoglobulin and ATGAM, there were no significant differences in clinically relevant adverse events between the two treatment groups. Malignancies were reported in 3 patients who received Thymoglobulin and in 3 patients who received ATGAM during the one-year follow-up period.

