### 3. TRIAL OBJECTIVES AND PURPOSE

Reflecting the last decades of clinical organ transplantation the accompanying immunosuppressive therapy developed from single and double to triple, quadruple, or sequential strategies using high-dose or low-dose regimens (6, 12, 13, 19, 21).

Recent multi-drug immunosuppressive protocols attempt to combine the advantage of different mechanisms of action by blocking signal or activation pathways of immunocompetent cells with a dose reduction of each single drug to decrease side effects (5).

Despite all these advantages rejections of allografts - especially steroid resistant rejections (SRR) - do occur and remain one of the major reasons for graft loss and patient death. Undoubtedly one of the most powerful weapons to treat rejection episodes are anti-lymphocytotoxic immunoglobulin preparations (7, 17), a treatment that is generally accepted worldwide for this indication.

The use of immunoglobulins (Ig) in prophylaxis is still in ongoing controversial discussion. The benefit of reducing the incidence of rejections, early graft loss, and dialysis after transplantation, in patients receiving Ig-induction therapy (2) faces arguments regarding necessity of general Ig-induction therapy, the waste of efficacious drugs for the management of SRR, higher rate of infections, and the costs of the treatment (23).

Considering only high-risk patients (i.e., patients who lost their graft due to immunological reasons or patients with high levels of panel reactive antibodies) an Ig-induction therapy is widely accepted, setting the costs of the therapy in relation to the improved outcome of these patients.

Nevertheless, it is desirable to reduce the costs furthermore. A possible way to save money might be the strategy of KADEN et al., who published his experience with a single bolus ATG-Fresenius S therapy in non-sensitised patients 1992 (8).

The bolus ATG protocol cannot, however, be adapted without further investigation, since another report (24) mentions a relatively high incidence of graft vascular thrombosis in patients who received a single high dose of ATG from another manufacturer.

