**6.3. Diagnosis and treatment of rejection episodes**

Clinical acute rejection episodes are defined by an increase of serum creatinine of >20% from baseline with consisting histology classified according to local practice.

Subclinical acute rejection episodes are defined by a protocol biopsy with consisting histology classified according to local practice.

The treatment of rejections is ad libidum of the physician, however, a cross-over treatment as rescue-therapy by using the immunoglobulin preparation (AFG-Fresenius S or Thymoglobulin) from the other group is prohibited.

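### The t-test on duration of rejection episodes cannot handle episodes that never reverse, and the protocol does not say when an episode ends (minor)

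*Protocol*

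**What the plan says.** Section 9 lists efficacy parameters with a test for each. One line is "Duration of rejection episodes (t-test"). The same list has "Rejection reversal rate (Chi-square statistic") and "12, and 24-months graft survival rate (Chi-square statistic"), and Section 9 also plans life tables for graft survival, patient survival and time to first rejection.

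The efficacy set is "all patients who were randomized and treated and for whom any post-treatment efficacy data are available". It carries no rule for an episode without an end date.

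Section 6.3 fixes how an episode is recognised: "Clinical acute rejection episodes are defined by an increase of serum creatinine of >20% from baseline with consisting histology classified according to local practice". Subclinical episodes are recognised on a protocol biopsy. Neither definition says when an episode is over.

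Section 3 says that rejections, steroid-resistant ones in particular, "remain one of the major reasons for graft loss and patient death". Section 9 opens by declaring every analysis in this pilot descriptive. Duration of rejection is not among the secondary endpoints in Section 4.3.2.

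**The concern.** Duration is a time from onset to end. The protocol expects some episodes not to reverse, since it analyses a reversal rate and names rejection as a cause of graft loss and death. For those episodes the time is either unobserved or stopped by another event. A t-test has no means of using such values, so they must be omitted or replaced by a number.

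Omission restricts the comparison to episodes that reversed, a group formed after randomisation and possibly by the treatment. An arm with more irreversible rejections then loses those episodes from the comparison. Replacement makes the mean depend on whichever end date is chosen.

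An SAP could define the end of an episode, but that alone would not let a t-test use censored or terminated durations, and the t-test is fixed in the protocol. At stake is a duration result that suggests similar arms in a trial whose stated expectation is equivalent efficacy.

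**Working it through.** **The plan's own figure.** The only design figure is 20 + 20 = 40 patients, set by feasibility. No mean, SD, alpha or power is given for this test, so there is nothing further to reproduce. What follows tests the mechanism on assumed data.

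**Worked example (assumed data, 10 episodes per arm).**
- Arm A, all reversed: 5, 6, 7, 7, 8, 8, 9, 9, 10, 11 days; mean 8.0, sum of squares about the mean 30.
- Arm B, six reversed: 5, 6, 7, 8, 9, 10 days; mean 7.5, sum of squares 17.5. Four never reverse.

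*Unreversed episodes dropped.* Pooled variance = (30 + 17.5)/14 = 3.39. Standard error = √[3.39 × (1/10 + 1/6)] = 0.951. t = 0.5/0.951 = 0.53 on 14 df, p = 0.61. B looks slightly better.

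*Cut off at graft loss, assumed on day 5.* B mean = (45 + 20)/10 = 6.5, sum of squares 32.5. Pooled variance = 62.5/18 = 3.47. Standard error = √(3.47 × 0.2) = 0.833. t = 1.5/0.833 = 1.80 on 18 df, p = 0.089, in favour of B.

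*Cut off late, assumed 700 days.* B mean = (45 + 2800)/10 = 284.5, p = 0.025, against B.

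*The protocol's reversal-rate test, 10/10 v 6/10.* χ² = 20 × (10×4 − 0×6)²/(10 × 10 × 16 × 4) = 5.0, p = 0.025 (Fisher 0.087).

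The same 20 episodes favour B, show nothing or count against B, depending on a rule the protocol does not give.

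**Simulation of the dropping rule.** Assumptions: 20 patients per arm; 25%, 40% or 60% rejecting in both arms; one episode each; reversed durations gamma with mean 8 and SD 4 days in both arms; all episodes reverse in A; 20%, 40% or 60% never reverse in B; 4000 runs per setting, skipping runs with fewer than two usable durations in an arm. Share of runs with p < 0.05:

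| Rejecting | t-test, unreversed dropped | Reversal-rate χ², 20% / 40% / 60% unreversed in B |
|---|---|---|
| 25% | about 5% throughout | 3% / 15% / 36% |
| 40% | about 5% throughout | 11% / 48% / 80% |
| 60% | about 5% throughout | 25% / 78% / 98% |

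The t-test stays near its nominal 5% however many episodes in B fail to reverse. If long episodes are the ones that fail (assumed means 8 v 12 days, 8 episodes per arm, over 14 days counted as unreversed), dropping them shrinks a 4-day difference to 1.6 days. The share with p < 0.05 falls from 31% to 14%.

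**How many such episodes?** The documents give no non-reversal rate. As an assumed stand-in, take one-year graft loss after rejection from Section 2.4.3: "day 30 and one-year post rejection graft survival (Thymoglobulin 83%, n=82; ATGAM 75%, n=80"), that is 17% to 25% lost.
- Highest cited rejection rates, 58% to 67% (Section 2.2.4): 20 × 0.58 × 0.17 = 2.0 to 20 × 0.67 × 0.25 = 3.4 per arm.
- Lower cited rates, 12.5% to 29% (same section): 20 × 0.125 × 0.17 = 0.4 to 20 × 0.29 × 0.25 = 1.5 per arm.

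Both ranges lean high, because that graft loss followed moderate, severe or steroid-resistant rejection.

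**The case against.** The strongest reply is that the plan already reports what the duration test misses. Reversal rate, graft survival, patient survival and number of prednisone pulses all have their own lines. Duration among reversed episodes, read with a reversal rate, is a coherent two-part description.

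This largely stands. With 12 episodes per arm, lognormal durations (median 10 days, log-SD 0.5) and assumed reversal of 95% v 60%, the t-test on reversed episodes gives p < 0.05 in about 4% of runs, a Mann-Whitney test ranking unreversed episodes longest in about 31%, and the plan's reversal-rate chi-square in about 56% (Fisher 36%). At an assumed 100% v 50% the figures are 4%, 57% and 93% (Fisher 82%). At 83% v 75%, every one of these tests is at 7% or below. None of these contrasts is a reversal rate from the documents, and the reversal-rate test is itself weak when few patients reject.

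A reader might infer that the protocol drops the worst rejections, or that the bias always favours the worse arm. No section says that unreversed episodes are excluded, and the example shows that the direction changes with the rule. A reader might also infer that irreversible rejection goes unanalysed, which the reversal-rate and graft-survival lines contradict.

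What the reply does not remove is that the protocol plans a between-arm test on duration by a method that cannot use these episodes, and nothing ties its reading to the reversal rate.

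**Conclusion.** The concern holds as a minor one. The t-test on duration is unsuited to episodes that do not reverse, and the end of an episode is undefined. The comparison is therefore either conditional on reversal or dependent on an arbitrary end date. That much rests on the text and on what a t-test requires.

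The size is uncertain. It depends on assumed durations and non-reversal rates: about 0.4 to 1.5 unreversed episodes per arm at the lower cited rejection rates, and 2 to 3 only at the highest. The consequence is confined to one potentially misleading line in a descriptive efficacy analysis of a 40-patient safety pilot. No sample size, primary result or decision rule depends on it.

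**What to change.** Add to Section 6.3 one sentence stating when a rejection episode is considered reversed. The criterion is for the investigators to choose.

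In Section 9, replace the t-test by time from onset to reversal of the first rejection, shown as cumulative incidence of reversal by arm, with graft loss and death as competing events and open episodes censored at the last visit.

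The minimum alternative is to keep duration as a descriptive summary among reversed episodes, always beside the number and proportion reversed in each arm, with no between-arm test.

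The cost is one definition and one changed line. Onset, reversal status, graft loss and death are already needed for other analyses in the list; the date of reversal is needed for any duration analysis, including the present one. With few episodes per arm the estimates will be imprecise, and the report should say so.
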